### Randomization and blinding

Randomization will occur in blocks of 2 and will be based on a table of random numbers generated in the online open program Openepi [32]. The random number table will be confidential. The packaging and distribution of the supplements will be performed by personnel not involved in the research. All researchers directly involved in the care and follow-up of the participating patients will not be aware of the supplements taken by the study patients. Unblinding may occur if requested by the assisting physician if a patient suffers clinical destabilization. The supplements will be delivered to the patients in metalized packages, sealed and identified by the name and code of the patient in the study, and it is not possible to identify the supplement as placebo or WP.

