### Sample size

Considering a muscle mass gain of 500 g in the intervention group at 12 weeks compared to the placebo group, with a standard deviation (SD) of 409.7 g, 11 patients in each group are required to guarantee 95% confidence and 80% power to the study. The results obtained in a similar study with WP supplementation were used as a reference [33].

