### Statistical analysis

Categorical variables will be presented as frequencies with percentages and will be compared using Fisher’s exact test and the chi-square test. Continuous variables will be presented as mean ± SD or median and interquartile range and will be compared using two-way analysis of variance (ANOVA) or Friedman’s test, whenever appropriate. A logistic regression analysis will be used to identify variables with an independent association with increase of lean muscle mass. A value of *p* < 0.05 will be considered statistically significant in all analyses. Calculations will be performed using the Statistical Package for the Social Sciences (SPSS 21.0 for Windows) program.

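### The added logistic regression for predictors of lean-mass gain asks more than 22 patients can support and dichotomises an outcome measured in grams

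*Protocol article*

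**What the plan says.** The Statistical analysis section of the protocol article has two layers. Continuous variables are compared by two-way ANOVA or Friedman's test. A separate model is then added: "A logistic regression analysis will be used to identify variables with an independent association with increase of lean muscle mass". The section gives no cut-point for a gain, no list of predictors and no limit on their number. Significance is judged at p "< 0.05 will be considered statistically significant in all analyses", and this model is not set apart as exploratory.

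The Sample size section treats muscle mass as continuous: "Considering a muscle mass gain of 500 g in the intervention group at 12 weeks compared to the placebo group". The SD it assumes is 409.7 g. It concludes that "11 patients in each group are required to guarantee 95% confidence and 80% power to the study". Allocation is 1:1 ("Randomization will occur in blocks of 2"), which makes 22 patients in all.

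**The concern.** Ordinary logistic regression needs a yes/no outcome, and looking for independent associations means fitting several predictors together. The article does not use the words dichotomised or multivariable, but its sentence leaves little room for another reading.

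Two things then go wrong:

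- A patient who gains 50 g and one who gains 1,500 g count as the same, although the outcome was recorded and powered in grams.
- The precision of a logistic model is limited by the smaller outcome class, not by the total. When one arm falls entirely on one side of the cut, the treatment odds ratio has no finite estimate. A combination of covariates that splits the outcomes perfectly does the same.

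The model concerns a main outcome. An infinite or very unstable odds ratio, or a list of independent predictors from such a fit, could be published beside the main result.

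**Working it through.** **Inputs.** From the article: difference 500 g, SD 409.7 g, 11 per group, alpha 0.05, power 80%. Assumed, because the article does not give them: a gain means change > 0; changes are normal with the same SD in both arms; the mean placebo change m runs from -500 to +500 g.

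**1. The plan's own figure.** n per group = 2 × (1.960 + 0.842)² × (409.7/500)² = 10.54, rounded up to 11. This reproduces the stated number (two-sided test, normal approximation), so the trial was sized on grams kept as grams.

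**2. A bound that needs no assumption about m or the cut.** The smaller of two classes among 22 patients is at most 11. That is at most 11/3 = 3.7 patients per predictor with three predictors, and 11/5 = 2.2 with five.

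**3. Chance of a gain.** p0 = Φ(m/409.7) under placebo; p1 = Φ((m + 500)/409.7) under whey protein. At m = 0, p0 = Φ(0) = 0.500 and p1 = Φ(1.220) = 0.889. Expected patients without a gain: 22 − 11 × (0.500 + 0.889) = 6.7.

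**4. Empty treatment cell.** An arm of 11 falls wholly on one side of the cut with probability q = p¹¹ + (1 − p)¹¹. At least one arm does so with probability 1 − (1 − q0)(1 − q1). At m = 0, q0 = 0.001 and q1 = 0.2736, giving 0.274.

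**5. Information lost.** With v(c) = Φ(c)(1 − Φ(c))/φ(c)², the large-sample efficiency of the yes/no comparison relative to the continuous one is 2/(v(c0) + v(c1)), where c0 = m/409.7 and c1 = (m + 500)/409.7. At m = 0: 2/(1.571 + 2.753) = 0.46, so 54% is lost. At m = +250: 2/(1.801 + 5.818) = 0.26, so 74% is lost. At m = -250: 2/(1.801 + 1.801) = 0.56, so 44% is lost.

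**6. Adding covariates.** This step was simulated with 1,000 trials per setting (Monte Carlo error up to about ±3 points), checking by linear programming for complete or quasi-complete separation. Covariates had no true effect. Binary ones had an assumed prevalence of 30%; the rest were continuous. Three predictors are treatment, one binary and one continuous; five are treatment, two binary and two continuous.

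| Placebo mean change | p0 | p1 | Smaller expected class | Empty treatment cell | Information lost | No finite estimate, 3 predictors | No finite estimate, 5 predictors |
|---|---|---|---|---|---|---|---|
| -500 g | 0.111 | 0.500 | 6.7 | 27% | 54% | 35% | 50% |
| -250 g | 0.271 | 0.729 | 11.0 | 6% | 44% | 15% | 24% |
| 0 g | 0.500 | 0.889 | 6.7 | 27% | 54% | 37% | 49% |
| +250 g | 0.729 | 0.966 | 3.3 | 70% | 74% | 81% | 86% |
| +500 g | 0.889 | 0.993 | 1.3 | 94% | 90% | 96% | 98% |

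**7. Sensitivity to the cut.** Only the distance between the cut and the mean matters. A cut at 500 g with a placebo mean of +250 g is therefore the -250 g row: 6% empty cells instead of 70%.

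**The case against.** The strongest reply is that this is a secondary model whose details a journal article may leave to a fuller plan, and that the alarming figures come from assumptions. Much of that stands. Several stronger readings are tempting but not supported:

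- **That the trial's main comparison is dichotomised and loses power.** On the same assumptions, Fisher's test on a yes/no gain has 43%, 33% and 11% power at placebo changes of -250, 0 and +250 g, against about 78% for a t-test on grams. But the article does not propose that test for the treatment effect; it keeps muscle mass continuous in ANOVA or Friedman's test.
- **That most patients will gain because both arms train.** The Background credits exercise with raising lean mass only in patients already depleted. The inclusion criteria do not require depletion, and the endpoint is framed as maintenance. A placebo mean of zero or below fits the article equally well.
- **That the model always discards most of the information and is often not estimable.** In the -250 g row the loss is 44% and an empty cell occurs in 6% of trials. A different cut-point can move a severe case to that row.
- **That it will yield extra false positives, or that predictors will be picked stepwise.** No false-positive rate was calculated, and no selection method is stated.

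What the reply does not remove is the bound of 11 in the smaller class. A fuller plan could name a cut-point and predictors, but it could not make 22 patients carry several of them. Even the mildest row gives 15% of trials without a finite estimate with three predictors and 24% with five.

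**Conclusion.** The point holds, confined to the additional model. The article commits to a logistic search for independent predictors in a trial where "11 patients in each group are required", on an outcome it measures and sizes in grams. Several predictors cannot be supported, whatever the cut-point.

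The extent is conditional. For a cut at change > 0 with the article's 500 g and 409.7 g, placebo mean changes of -250, 0 and +250 g give an empty treatment cell in about 6%, 27% and 70% of trials with treatment alone, and an information loss of about 44%, 54% and 74%. These rest on normal changes, equal SDs and all 22 patients being analysed. The conclusion about the main group comparison of muscle mass is untouched. The change is worth making because it is cheap and the model bears on a main outcome, but it is not a flaw in the primary analysis.

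**What to change.** In the Statistical analysis section, replace the logistic regression sentence with a linear regression of continuous week-12 muscle mass (or its change) on treatment and baseline muscle mass, with at most one further covariate named in advance. Report estimates with 95% confidence intervals and label the model exploratory.

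This costs one sentence and no new data, since body composition is already measured at baseline and week 12. The downside is that results are in grams, not odds of a gain, and fewer candidate predictors are examined.

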### Ethics and dissemination

The study was submitted and approved by the Ethics and Research Committee of the National Institute of Cardiology, in Rio de Janeiro, Brazil and the participants will sign the free and informed consent form. Any modifications that are made to the study will be immediately reported to the Ethics Committee responsible for approving the trial. A Data Monitoring Committee (DMC) will not be needed as this is a single-center trial. To ensure the confidentiality and the safety of participants, all information about participants will be stored safely in a computer with access restricted to the study’s investigators and, if any harm occurs, patients will have full access to free treatment at the National Institute of Cardiology, which belongs to the Brazilian public healthcare system.

Throughout the trial, the partial results will be presented at national and international scientific congresses. This study will contribute significantly to the academic training of health professionals in the area of cardiovascular sciences, committed to the production of knowledge and critical reflection, and generate new interventions capable of optimizing the treatment and quality of life of patients with HF. At the end of the study the results of the study will be published in scientific journals and presented at scientific meetings.

### SPIRIT

This protocol has been written in accordance with the Standard Protocol Items: Recommendations for Interventional Trials (SPIRIT) guidelines. The SPIRIT Checklist is in Additional file 1. The SPIRIT Figure is in Fig. 2.

**Fig. 2 Fig2:**
[figure not shown]
Standard Protocol Items: Recommendation for Interventional Trials (SPIRIT): the schedule of enrollment, interventions, and assessments

## Discussion

The proposed study is a double-blind, randomized, placebo-controlled clinical trial aimed at investigating the effects of WP supplementation associated with 12 weeks of supervised exercise in maintaining muscle strength in patients with HF. Advanced HF is often associated with severe loss of body weight and especially of muscle mass, and it is an important cause of hospitalization and one of the most important health challenges since its prevalence tends to increase with the aging of the population and the increase in the survival of patients who have suffered acute coronary events. It is an ongoing epidemic problem, resulting in a high socioeconomic cost, represented by the expenditure on medicines, repeated hospitalizations, loss of productivity, early retirement, possible surgeries and, ultimately, the need for heart transplantation. In this sense, it is of great importance to carry out studies that evaluate the possible benefits of new clinical and nutritional interventions for HF patients, favoring the development of new treatment strategies.

### Trial status

Patient recruitment is currently being undertaken.

## Abbreviations

APU: Arbitrary perfusion units
CPET: Cardiopulmonary exercise test
CR: Cardiac rehabilitation
CVC: Cutaneous vascular conductance
DMC: Data Monitoring Committee
ECG: Electrocardiogram
ECW: Extracellular water
HF: Heart failure
ICW: Intracellular water
LVEF: Left ventricular ejection fraction
MFC: Maximal functional capacity
MLHFQ: Minnesota Living with Heart Failure Questionnaire
NYHA: New York Heart Association
PORH: Post-occlusive reactive hyperemia
SPSS: Statistical Package for the Social Sciences
TBW: Total body water
WP: Whey protein
